## Abstract

**Background:**

In the emergency department (ED), medical procedures, such as arterial blood gas (ABG) testing, can cause pain and high stress levels. However, ABG testing is a routine procedure assessing the severity of the patient's condition. To reduce the pain of ABG, several methods have been investigated without significant difference in pain perception. Communication, a key element of care, has shown a significant effect on pain perception. A positive communication strategy, including positive, kind, or reassuring words, can reduce pain perception, while negative words can raise this perception, causing discomfort, known as the “nocebo effect.” Although some studies have compared the impact of verbal attitudes, particularly in anesthesia and mainly with staff already trained in hypnosis, to the best of our knowledge, none have investigated the effect of communication in the emergency setting, where patients may be more suggestible to the words used.

**Objective:**

In this study, we will investigate the effect of positive therapeutic communication on pain, anxiety, discomfort, and global satisfaction in patients requiring ABG compared to nocebo and neutral communication.

**Methods:**

A single-center, double-blind randomized controlled trial (RCT) with 3 parallel arms will be conducted with 249 patients requiring ABG during their ED visit. Patients will be randomly assigned to 1 of 3 groups before receiving ABG: positive communication group, negative communication (nocebo) group, or neutral communication (neutral) group. The communication and the words used by the physicians during hygiene preparation, artery location, and puncture will be imposed in each group. The study will be proposed to each patient corresponding to the inclusion criteria. The physicians will not be trained in hypnosis or in positive therapeutic communication. The procedure will be recorded with audio recorders to test its quality. Intention-to-treat analysis will be performed. The primary endpoint is the onset of pain. The secondary outcomes are patient comfort, patient anxiety, and global satisfaction of the patient with the communication strategy used.

**Results:**

On average, 2000 ABG procedures are performed each year in the EDs of hospitals. In this study, 249 patients are expected to be included. With a projected positive response rate of 80%, we intend to include 25 (10%) patients per month. The inclusion period began in April 2023 and will run until July 2024. We hope to publish the results of the study during the fall of 2024.

**Conclusions:**

To the best of our knowledge, this study is the first RCT assessing the use of positive communication on pain and anxiety in patients undergoing the ABG procedure in the ED. A reduction in pain, discomfort, and anxiety is expected when using positive communication. If the results are positive, this could be useful to the medical community and encourage clinicians to monitor their communication during care.

**Trial Registration:**

ClinicalTrials.gov NCT05434169; https://clinicaltrials.gov/ct2/show/NCT05434169

**International Registered Report Identifier (IRRID):**

PRR1-10.2196/42043

## Introduction

Pain, defined as a disagreeable sensory or emotional experience, is the most frequent symptom among patients admitted to the emergency department (ED). Karwowski-Soulié et al [1] estimate that this symptom can be observed in almost 80% of patients upon their arrival to the ED. Despite several international recommendations concerning pain management [2,3], pain in the context of an emergency often remains underestimated [4]. Medical procedures, such as venous or arterial blood collection, which are essential for diagnostic management and patient care, can also generate pain and a high level of stress for patients who are already weakened by their underlying condition [5]. This is known as “care-related pain” [6].

Arterial blood gas (ABG) sampling is necessary to assess the gravity of the patient’s condition and is a procedure conducted routinely in the ED. In a medium-size hospital (30,000 hospitalizations per year), approximately 1000 ABG tests are conducted annually [7]. However, arterial blood collection is generally associated with pain and patient anxiety [8].

To decrease the perception of pain linked to the collection of arterial blood, several methods have been studied, such as applying a topical anesthetic cream (eg, lidocaine, xylocaine) or administering a subcutaneous injection of lidocaine prior to the procedure [9]. Given that arterial blood collection is often performed in emergency situations and that the anesthetic cream must be applied at least 1 hour before sampling, this method is not adapted to emergency practices. In a previous study, a subcutaneous injection of lidocaine did not allow a significant reduction in pain during radial artery puncture [10]. Similarly, another study using ultrasound guidance for arterial blood sampling did not show any significant decrease in pain, the rate of immediate complications, or physician satisfaction [11].

In addition to the therapeutic tools commonly used, communication is a key element of care [12]. In routine practice, caregivers inform patients that they are going to perform a potentially painful act. However, forewarning a patient that one will perform a painful act increases the perception of pain [13]. It has also been shown that a communication strategy including the use of positive, kind, or reassuring terms (“Let me reassure you…,” “Are you comfortable?,” “Are you warm enough?”) can contribute to decreasing pain [14,15], while conversely, the choice of terms with a negative connotation (“Okay, this might sting,” “Do not panic,” “Are you in pain?,” “Are you cold?”) may increase the perception of pain and provoke a sense of discomfort [16]. In the latter case, this is known as the “nocebo” effect [15]. A communication strategy including reassuring terms, perceived by the brain as agreeable information, can reduce the pain perception. The objective of this strategy is that the painful message becomes less present as much as possible and that the patient benefits from a feeling of control. This procedure is widely used in hypnosis communication [17] and is based on a neurobiological rationale [18,19], that is, an increase in the secretion of endogenous opioids [20-25] affecting pain modulation networks [26] decreases transmission in the pain pathways [27,28], thus leading to a release of dopamine in the striatum [29]. This technique has already been shown to be of benefit in patient management [15,30] in various domains, such as anesthesia and pediatrics [15,31].

Arrival to the ED can induce a particular state of consciousness linked to anxiety and a heightened suggestibility of negative communication. Although several studies have compared the impact of verbal attitudes, notably in the domain of anesthesia and mainly with staff already trained in hypnosis, to the best of our knowledge, none have studied the effect of positive communication by caregivers or physicians among a patient population in the ED setting. Given the limited therapeutic options to relieve the pain and discomfort of blood collection performed in the ED, this study will investigate the effect of positive therapeutic communication on pain, anxiety, discomfort, and global satisfaction in patients requiring ABG compared to nocebo or neutral communication.

## Methods

### Study Design

This study will be a single-center, double-blind randomized controlled trial (RCT) with 3 parallel arms. To minimize bias during the intervention itself, the communication strategy will be clearly defined beforehand. The evaluator (any person [physician/student/other] assessing patient outcomes before and after arterial blood collection but playing no role in patient management in the ED or in the conducting of the procedure and without any knowledge of the study arm assigned to the patient at randomization) will be blinded to the strategy used.

### Setting

Patients will be recruited at the adult ED of the Cantonal Hospital of Fribourg (HFR) in Switzerland. On average, 2000 ABG procedures are performed each year in the ED of the HFR.

### Population and Sample

The inclusion criteria are as follows:

Patients over 18 years of agePatients scheduled to undergo radial artery blood collection during their visit to the ED in order to pursue routine careFree and informed consent obtained from the patient

The exclusion criteria are as follows:

Patients incapable of judgmentPatients with conditions that render them unable to participate in the intervention in this study (eg, cognitive impairment, major hearing loss without the use of hearing aids, acute psychiatric disorders, under intravenous or oral sedation)Patients with an insufficient understanding of the French language, as defined by self-evaluationPatients in critical situation requiring immediate resuscitationLocal anesthesia (subcutaneous, transdermal patch) at the point of ABG puncturePatients already treated with anxiolytics or sedatives during care in the ED

#### Recruitment and Screening

Potentially eligible patients for inclusion in the study will be identified by residents who will inform the senior physician responsible for triage (triage doctor [TD]) in the ED at the initial stage of patient management if arterial blood collection is required for medical care. The senior TD (triage medical consultant regulating the flow of activity in the ED, who can be a physician investigator) will proceed with recruitment as follows: “We have explained to you that we need to perform a blood gas test on a sample of blood from the wrist artery. At present, we are conducting a study to examine the patient experience with this procedure. In this context, if you accept to participate in our study, another person will ask you some questions before and after sample collection. You are free to participate and to withdraw at any point of time during the study. If you refuse, there will be no modification of your care in the ED. The data collected will be coded, and your name or any other personal information that could identify you will be removed. The entire procedure will be recorded using an audio recorder.”

The study will be proposed to all eligible individuals from among participants available 24 hours a day, 7 days a week. With a projected positive response rate of 80%, we intend to include 25 patients per month. To achieve the desired sample size, we would need 12 months to finalize study inclusion.

### Data Collection

The clinician in charge of the patients will determine the indication for ABG testing according to the rules of good practice in emergency medicine (hypotension and shock, dyspnea and respiratory insufficiency, intoxication, metabolic and acid-base disorders, renal insufficiency, polytrauma, convulsions, disorders of the state of consciousness). Patients in critical situations requiring immediate resuscitation will be excluded from the study because of the impossibility of waiting for the time necessary for screening/inclusion/randomization before ABG testing, the immediate vital prognosis being engaged.

Following verification of the inclusion criteria and patient agreement, the patient will be included in the study by the senior MRT. The latter will collect written signed informed consent forms after the procedure, which will be stored in a dedicated file cabinet and locked by 1 of the physician investigators (physicians with a role in the concept, implementation, or organization of the study). The forms will then be filed in a file reserved for this purpose and stored in a secure location by the physician acting as the principal investigator (PI).

Next, the patient will be randomized to 1 of the 3 study arms by an administrative reception agent, who will use Research Electronic Data Capture (REDCap) software (Vanderbilt University) to assign the patient to a randomization arm. To maintain the blinding of those involved in the study, the administrative reception agent will give the participating physician an opaque envelope containing randomization arm details and an audio recorder. The participating physician (resident performing arterial blood collection, who can concomitantly manage the medical aspect of the patient) will only be able to open the envelope once they are in the patient booth in order to maintain the blinding of the senior MRT. They will perform arterial blood collection according to the communication method generated by the randomization arm and will be the only person aware of the patient groups.

The senior MRT will also communicate the patient ID to the evaluator. Data collection, as well as the case report form (CRF), will be completed by the evaluator before the beginning of the recording and after completion of the procedure. Data will be collected with the help of the electronic patient record and the questions asked to the patient before and after the ABG procedure. Thus, the patient will be blinded to the specific intervention status.

### Case Report Form

The following data will be collected and included in dedicated CRFs. The paper CRF will contain a first part with the date of the screening, the name of the medical officer who will perform the screening, the inclusion and exclusion criteria, whether the patient has been informed orally, and whether they have provided oral consent. The medical officer will confirm whether the inclusion and exclusion criteria have been met and, if so, indicate the number of the envelope containing the random allocation to 1 of the 3 study arms; this number will be the patient's ID in the study.

Once the patient is included in the study, the assessor will fill in the second part of the paper CRF before the ABG procedure: the name of the assessor, educational level, native language (French/Swiss German/German/Italian/Portuguese/other), tobacco, diabetes, first 3 outcomes, vitals (blood pressure, heart rate, respiratory rate), and time data on the ABG procedure.

After the ABG procedure, the evaluator will fill in the third part of the paper CRF, containing the 5 outcomes, the level of overall satisfaction, the vitals (blood pressure, heart rate, respiratory rate), the number of arterial punctures observed on the skin, and the type of words used by the doctor during the procedure according to the patient.

The fourth part of the paper CRF certifies that the patient has received the complete information about the study, whether the patient has consented, and, if they have consented, whether they have received a copy of the signed informed consent form.

The fifth part of the paper CRF contains the following information extracted directly from the patient's file: age, sex, first and last names of the attending physician, duration of the ED visit (difference between admission and discharge from the ED, difference between admission to the ED and the patient's placement in the cubicle), reason for admission to the ED (Swiss emergency triage scale [U1-U4]), list of emergency reasons, BMI (weight/(height in m × height in m), and the patient outcome after the emergency stay (inpatient/outpatient/death).

The evaluator will confirm the accuracy of the data collected.

### Intervention Groups

During each step of the sampling (identification, disinfection, sampling) for the ABG procedure, the physician involved will communicate with the patient with a preestablished speech according to the assigned study arm. Communication sentences for each intervention group are presented in Table 1. In the case of failure of the first puncture, the intervening doctor will be able to use the second set of sentences corresponding to the assigned intervention group (also in Table 1).

**Table 1 table1:** Study arms.

Study arm	Intervention/treatment
Positive therapeutic communication: Solicit the subconscious mind of the patient by asking questions that are not focused on the ABG^a^ procedure. This process allows to divert the attention of the brain to more pleasant information and thus modulate the painful information. This is a standardized intervention with precise phrases.	The positive therapeutic communication group physician will say: During identification of the arterial blood collection site: “Are you comfortably installed?,” “How old did you say you were?,” etc At the time of disinfection: “How did you get to the hospital?,” “What day is it?,” etc At the time of puncture: “What is the noise of the lights at your home?,” “Does your car still go to the shops?,” etc
Nocebo: Use of words with a negative connotation (words used frequently in daily practice in the ED^b^)	The nocebo group physician will say: During identification of the puncture site: “That’s where I am going to prick you,” “I am looking for the place where I will prick,” etc At the time of disinfection: “Watch out, it is cold,” “It is disagreeable,” “I am disinfecting the site,” etc At the time of puncture: “Watch out! I am going to prick…1, 2, 3…I am pricking,” “Watch out, this is going to hurt, I am pricking,” etc
Neutral: Use of words defined as neutral (ie, no negative or positive connotation but based on the description of precise facts)	The neutral group physician will say: During identification of the site: “I am taking your pulse,” “I am identifying the artery,” etc At the time of disinfection: “I am disinfecting the site,” “I am cleaning your skin,” etc At the time of puncture: “I am taking the sample,” “I am performing the puncture,” etc

^a^ABG: arterial blood gas.

^b^ED: emergency department.

#### Positive Therapeutic Communication Arm

The first 2 sentences allow the gesture to be accompanied by reassuring words and positive words, while the last sentence involves the patient's subconscious by asking a question not focused on the procedure (confusion). This allows the brain to divert attention to more pleasant information and thus modulate the painful perception.

A study of a similar design, “Hypnosis and Communication Reduce Pain and Anxiety in Peripheral Intravenous Cannulation: Effect of Language and Confusion on Pain During Peripheral Intravenous Catheterization” (KTHYPE) [15], has already evaluated the impact of these sentences during the placement of a venous catheter in patients undergoing surgery and demonstrated its beneficial effects.

All the short phrases in this protocol are inspired by the KTHYPE study and have been adapted for the population and context of our study.

#### Nocebo Arm

The use of words with negative connotations would cause more pain and anxiety [13,18]. Warning a patient that they are going to undergo a potentially painful procedure can potentiate discomfort. In current practice, these are the words most used by emergency teams. The stress associated with the emergency consultation could further amplify the painful experience and the impact of these words by the state of hypersuggestibility that it induces.

#### Neutral Arm

The use of neutral terms allows precisely describing the procedure to the patient and informing them of the course of the treatment without using words with negative connotations (pain, stinging, unpleasant).

### Hypotheses

The principal hypothesis is as follows: Pain perceived during the collection of an arterial blood sample in the ED is lower when it is performed using positive therapeutic communication compared to neutral or nocebo communication.

The secondary hypotheses are as follows:

Discomfort perceived during the collection of an arterial blood sample in the ED is lower when the procedure is conducted using positive therapeutic communication compared to neutral or nocebo communication.Anxiety perceived during the collection of an arterial blood sample in the ED is lower when the procedure is conducted using positive therapeutic communication compared to neutral or nocebo communication.

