### Statistical Analysis

#### Sample Size Calculation

With a significance level of .05, a power of 0.9, a difference in pain on the VRS of 1.5 (generally accepted as clinically significant) with an expected SD of 2.5 [35], and an attrition of 20% on the basis of a group-independent *t* test (a specific case of linear mixed effects models [LMMs]), we must include 83 patients in each group to show the efficacy of the intervention on pain by applying the Bonferroni correction (ie, a total of 249 patients).

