#### Statistical Analysis Plan

First, descriptive statistics (frequencies and percentages for categorical data; means, SDs, medians, and IQRs for quantitative data) will be run for each measure of time for each group and the overall study sample. In addition, an analysis of nonresponses and patient dropouts will be conducted. Second, bivariate associations will be calculated to compare the groups at baseline (Pearson chi-square test, Fisher exact test, *t* test, and the Mann-Whitney test according to the distribution of variables). Third, to test the impact of the intervention on the different outcomes (hypotheses 1, 2, and 3), LMMs with patients, groups and physicians as a random effect will be performed to analyze changes over time. The participation of approximately 25 physicians is foreseen in this study. The models will be tested on all available data.

The effects of time, groups, and their interaction will be tested by controlling for sociodemographic characteristics and variables linked to health status. An intention-to-treat (ITT) analysis, per protocol (PP) and based on the analysis of communications (ie, the respect of the quality of the defined communication according to the protocol; see the next section), will be conducted. The Pearson chi-square test comparing the allocation defined in the protocol and the allocation following the analysis of communications will be performed. If necessary, a generalized LMM will also be used to explore the differences between the available measured variables (physicians having performed the ABG procedure, pain, etc). Statistical analysis will be performed on available data, and no imputation of missing data will be conducted. Given that our study will be conducted on a 1-to-1 basis with a member of the research team and on the basis of previous experience, we expect that the number of missing values will be low. Statistical analyses will be performed using the R (R Core Team and the R Foundation for Statistical Computing) and STATA version 12 (StataCorp); the level of significance will be set at *P*=.05.

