### Conclusion

The Positive Therapeutic Communication on Pain (POPAIN) trial is an RCT assessing the effect of positive communication on pain, discomfort, and anxiety in patients undergoing ABG testing compared to neutral and nocebo communication. A reduction in pain, discomfort, and anxiety is expected when using positive communication. These results could be useful to the medical community and encourage clinicians to monitor their communication to reduce pain and anxiety in care. This method, if successful, could be easily implemented in other emergency departments.

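### The stated test of pain (three-arm group and interaction effects at .05) matches neither the directional hypothesis nor the Bonferroni-corrected pairwise sample size, so its wording permits a nocebo-only difference to be read as benefit of the positive script

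*Protocol article*

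**What the plan says.** **Hypotheses.** Pain during arterial sampling "is lower when it is performed using positive therapeutic communication compared to neutral or nocebo communication". The two secondary hypotheses use the same *or*, as does the last paragraph of the Introduction. The abstract's Objective and the Conclusion name the same two comparators joined by *and*. No section says whether positive must beat one comparator or both.

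**Statistical Analysis Plan.** To test hypotheses 1 to 3 with mixed models, "The effects of time, groups, and their interaction will be tested by controlling for sociodemographic characteristics and variables linked to health status". At the end of the section, "the level of significance will be set at" P=.05. No contrast between arms is named, and no multiplicity adjustment is mentioned.

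**Sample Size Calculation.** "With a significance level of .05, a power of 0.9, a difference in pain on the VRS of 1.5", an expected SD of 2.5 and 20% attrition, based on a two-group t test with a Bonferroni correction. The result is 83 per arm and 249 in total. The number of comparisons is not stated.

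**Nocebo Arm.** "The use of words with negative connotations would cause more pain and anxiety"; the section also describes this wording as the most used by emergency teams at present.

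**Conclusion.** "A reduction in pain, discomfort, and anxiety is expected when using positive communication".

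**The concern.** The hypothesis concerns one arm and one direction: positive is lower. With three arms, the group effect and the group-by-time interaction each have two degrees of freedom and no direction. They can be significant because any one arm differs from the others, and the article itself expects one arm, nocebo, to differ by raising pain.

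The neutral arm is the only one that can separate two explanations of a difference between positive and nocebo: that positive words relieve pain, or that negative words cause it. Neither the hypothesis nor the stated test gives the neutral arm that role. If neutral wording did as well as the positive script, the practical lesson would be to avoid negative words. The results could nevertheless be presented as an effect of positive communication.

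**Working it through.** **Inputs.** Difference 1.5, SD 2.5, power 0.90, alpha .05, attrition 20% and 83 per arm are from Sample Size Calculation. Two-sided testing is assumed, because sidedness is not stated. Evaluable patients per arm: 83 × 0.8 = 66.4, taken as 66; 83 is the case of no attrition.

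**1. Reproducing 83 per arm.** With two comparisons, alpha is .05/2 = .025 two-sided.

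n = 2 (z₀.₉₈₇₅ + z₀.₉₀)² (SD/difference)² = 2 × (2.241 + 1.282)² × (2.5/1.5)² = 68.95, so 69.

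69 × 1.2 = 82.8, so 83, which is an exact match. With no correction, n is 59, inflated to 71 (× 1.2) or 74 (÷ 0.8). With three two-sided comparisons it is 76, inflated to 92 or 95. Two pairwise comparisons at .025 are therefore the most natural origin of the figure.

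**2. Overall three-group test when positive equals neutral.** Means are (0, 0, d), where d is the assumed nocebo excess.

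λ = n Σ(μᵢ − μ̄)² / SD² = n × (2/3) d² / 6.25, with F on 2 and 3n − 3 degrees of freedom at .05.

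| d | n per arm | λ | P(significant) |
|---|---|---|---|
| 1.5 | 66 | 15.84 | 0.952 |
| 1.5 | 83 | 19.92 | 0.984 |
| 1.0 | 66 | 7.04 | 0.651 |
| 1.0 | 83 | 8.85 | 0.758 |

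**3. Pairwise contrasts in the same scenario, d = 1.5.** For positive versus nocebo, the noncentrality is (1.5/2.5) √(n/2): 3.45 at n = 66 and 3.87 at n = 83. Power of a two-sample t test at two-sided .025 is 0.88 and 0.94. Positive versus neutral comes out in favour of positive in .025/2 = 1.25% of trials (1.2% to 1.3% by simulation). Under an either-comparator rule, success would thus come almost entirely from the nocebo arm.

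**4. Group-by-time version.** Steps 2 and 3 use a single post-procedure score. For change from before to after, the SD is 2.5 √(2(1 − ρ)), with ρ the before/after correlation. The article does not give ρ, so a range is assumed. Results are for n = 66 and d = 1.5; the pairwise column uses the normal approximation.

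| ρ | SD of change | Overall test at .05 | Positive vs nocebo at .025 |
|---|---|---|---|
| 0.3 | 2.96 | 0.857 | 0.75 |
| 0.5 | 2.50 | 0.952 | 0.89 |
| 0.7 | 1.94 | 0.997 | 0.99 |

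At ρ = 0.5 the change score has the same SD as the single score, so the overall result equals that of step 2.

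**The case against.** The strongest reply is that pairwise contrasts were intended all along. An overall test needs no Bonferroni correction, and 83 per arm reproduces with exactly two comparisons. Lower compared with neutral or nocebo can be read as lower than each, and the Objective and Conclusion say *and*; on that reading, a tie between positive and neutral refutes the hypothesis. A three-level group factor in a mixed model also yields pairwise coefficients, and the planned descriptive statistics by group would make such a tie visible. Finally, naming contrasts is often left to a statistical analysis plan, which is not shown here.

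Much of this stands. A reader might infer that the trial would declare its hypothesis met in about nine of ten trials in which positive is no better than neutral. The documents do not support that. The article never makes a significant overall or interaction test its criterion of success, and the probabilities become false claims only under the overall-test or either-comparator reading. Nor does it say that positive communication should be adopted: it says the results could be useful and that the method, if successful, could be implemented elsewhere. A win over nocebo also has meaning of its own, since that wording is described as current practice.

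The reply does not remove the mismatch. The article is not silent on the test: it states one, with a level of .05, and both differ from the basis of its own sample size. The Bonferroni correction does not settle the reading either. It fits a rule under which either comparison may succeed, whereas a rule requiring both would need no split.

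**Conclusion.** The point holds as an inconsistency between three parts of the article: a directional hypothesis with an unclear *or*, a non-directional three-arm test at .05, and a sample size built on Bonferroni-corrected pairs. The wording permits, but does not prescribe, treating a difference produced by nocebo alone as evidence for the positive script.

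The size depends on the assumed harm of nocebo wording. The 1.5 points are borrowed from the target difference, because the article gives no nocebo effect. At 1.0 point the risk is clearly smaller but still substantial. For the group-by-time test it also depends on the unstated before/after correlation. None of the calculations include covariate adjustment or the physician effect.

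**What to change.** - In Statistical Analysis Plan, name positive versus neutral and positive versus nocebo, as group-by-time contrasts for pain, as the confirmatory tests. Test each at the two-sided .025 already implied by the sample size. Keep the overall group and interaction tests as descriptive support.
- In Hypotheses, replace *or* by the *and* of the Objective and Conclusion.
- State in advance what each contrast supports. A claim of benefit for the positive script itself needs positive versus neutral. A win over nocebo alone is reported as better than the negative wording in current use, with the neutral-versus-nocebo estimate beside it.

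If positive equals neutral, the chance of wrongly claiming benefit for the positive script is then 1.25%, whatever nocebo does. Power for positive versus neutral at a true 1.5 points is 0.88 with 66 per arm and 0.94 with 83 (single-score basis), close to the planned 0.90.

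The cost is wording in the hypothesis and analysis plan, with no extra patients or data. The small downside is a narrower headline claim if only the nocebo contrast succeeds. The change should be dated and settled before any unblinded analysis.
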